#### Study outcomes

Study outcomes include measurements at the levels of body functions and structures, activities and participation as defined by the International Classification of Functioning, Disability and Health (ICF) [29]. Environmental characteristics (school type and home status) are assessed at baseline. Demographic variables (age, weight and arm span), the use of medication (such as corticosteroids), any co-interventions and daily amount of physical activity are registered during each session.

The assessments of boys in the intervention group are conducted during the baseline period (T0: at baseline; T1: after 4 weeks; T2: after 8 weeks), the training period (T3: after 12 weeks; T4: after 24 weeks) and the follow-up (T5: 4 weeks after the end of the training; T6: 24 weeks after the end of the training). The assessments of boys in the control group are conducted during the baseline period (T0: at baseline; T1: after 4 weeks; T2: after 8 weeks), the control period (T3: after 12 weeks; T4: after 24 weeks), the subsequent training period (T5: after 12 weeks of training; T6: after 24 weeks of training) and during the follow-up (T7: 4 weeks after the end of the training). Assessments take place at the department of Rehabilitation of the Radboud University Nijmegen Medical Centre (T0, T2, T4, T6), but also at home (intervention group: T1, T3, T5; control group: T1, T3, T5, T7) to reduce the practical burden on the participants. All data are collected by the (trained) primary investigator (MJ). (figure 4)

**Figure 4 F4:**
[figure not shown]
**Measurements study 1**. BP (Baseline period), IP (Intervention period), FU (Follow-up), CP (Control period)

##### Primary outcomes

Bicycle ergometry: Six-Minute Bicycle Test

Muscle endurance, in this study defined as 'the ability to sustain a power without the occurrence of peripheral fatigue', is assessed with an adjusted and modified bicycle ergometer test for both the lower and upper extremities. Bicycle ergometry has been used in many studies to examine the (an)aerobic performance in healthy children and children with disabilities, and several exercise protocols are available. However, these protocols are not feasible for boys with DMD, since large muscle groups are affected in DMD and initial load and subsequent increments of load are often too hard to sustain for these patients[7,30]. Muscle endurance is, therefore, examined with a recently developed motor-assisted (passive mode 1, no-load speed 7 RPM) Six-Minute Bicycle Test by which boys are instructed to cycle as fast as possible i.e. to make as many cycling revolutions as possible. Boys start with a test for their legs and, thereafter, perform the same (arm cranking) test with their arms.

The occurrence of muscle fatigue during bicycle ergometry is assessed objectively with bipolar surface electromyography (sEMG), since peripheral fatigue is reflected as an increase in the amplitude and a decrease in the median frequency of the sEMG signal[31,32]. These parameters were found to be responsive to changes in muscle endurance during an exercise program[33,34]. Electrodes are placed unilaterally (right leg, right arm) on the m. rectus femoris, m. vastus medialis, m. biceps femoris, m. tibialis anterior, m. biceps brachii, m. triceps brachii and m. deltoideus. Electrode placement procedures will follow the recommendations for Sensor and Sensor Placement Procedures for surface electromyography[35]. Data will be registered with an EFA system (Twente Medical Systems International). The occurrence of muscle fatigue is also assessed subjectively with the OMNI Scale for perceived exertion[27]. The OMNI Scale is reliable and valid over a wide range of dynamic exercise intensities in children[27,36].

Motor Function Measure

The MFM is a recently developed instrument to assess motor function in ambulant and non-ambulant patients with neuromuscular diseases (NMD) aged 6-62 years[37]. The MFM has shown excellent internal consistency and good to excellent intra- and interrater reliability in French neuromuscular patients[37]. Vuillerot et al.[38] showed that the MFM is able to measure changes in motor function over time in boys with DMD. An ongoing study examines validity and applicability of the MFM in rehabilitation institutes in the Netherlands.

##### Secondary outcomes

Table 2 shows an overview of the secondary study outcomes and their psychometric properties.

**Table 2 T2:** Outcome measures and psychometric properties

Level	Study outcome	Measurement tool	Psychometric properties	Assessment
**Body structures and functions**	Muscle endurance	Six-Minute Bicycle Test*	Feasible for ambulant and non-ambulant boys with DMD (pilot study, unpublished data)	T0, T2, T5

	Joint mobility (PROM)	Goniometry[55] (knee ext*, ankle dfl*, shoulder abd*▪, elbow ext*▪, wrist ext▪, wrist radial and ulnar dev▪)	Standardized methods are feasible[56] and have good intra- and inter-rater reliability in DMD[57] Passive wrist radial deviation is correlated with functional hand activities[58] and lower extremity contractures are related to onset of wheelchair reliance in DMD[4]	All

	Muscle strength	Modified MRC[59] (hip ext*, knee ext* ankle dfl*, shoulder abd*▪, elbow ext*▪, wrist ext▪)	Moderate to good intra-rater reliability[59] and acceptable inter-rater reliability in DMD after a training session[60] Muscles with MRC grade 4 or 5 are difficult to measure with MMT, but muscles with MRC grade ≤3 are more difficult to measure with HHD[4]	All

	Muscle atrophy, intra-muscular fibrosis and fatty infiltration	Quantitative skeletal muscle ultrasonography (muscle thickness and echo intensity) [61]: RF, TA, BB, FF*▪	Good inter-rater agreement in children[62] High predictive values to discriminate between children with and without a NMD[63]	T2, T5, T6/T7*

	Bone density	Dexascan (femur and lumbar spine)*	Changes in bone mineral density can be detected with confidence in healthy boys ≥10 years after 6 months and in younger boys after 12 months[64], but a change in body shape may influence scan results[65]	Conventional protocol for each boy

	Incidence of fractures	Semi-structured interview*		All

**Activities**	Functional abilities	Motor Function Measure[37] (D1*, D2*, D3*▪)	Excellent internal consistency for the global scale and the subscales in NMD[37] Excellent to moderate intra- and inter-rater reliability in NMD[37] Good face validity, convergent validity and discriminant validity in NMD[37] Sufficiently sensitive to detect changes in the total score in DMD[66] Total score predicts loss of ambulation in DMD[67]	All

	Upper limb function	Action Research Arm Test[40,41] ▪	Excellent intra-rater, inter-rater and test-retest reliability in stroke patients[40,41] Highly correlated with the Fugl-Meyer score^47 ^and Functional Independence Measure^48 ^in stroke patients Suitable to detect changes over time in stroke patients[42]	All

	Functional abilities (grading)	Vignos* and Brooke Scale*▪ [56]	Good inter-rater and intra-rater reliability[57,57] and correlated with timed tests[46,68,69] in DMD	All

	Functional mobility	Functional Mobility Scale[70] *	A clinically feasible, valid and reliable tool in CP[70,71]	All

	Functional abilities (timed tests)	Timed and graded functional tests (and total GSGC score) [72]: walk 10 meters, climb 3 stairs, rise from the floor and rise from a chair*	Good to excellent intra- and inter-rater reliability in DMD[57,73] Sensitive to change in DMD: a small reduction in muscle force was accompanied by a large increase in time it takes to complete functional tests[74]	All (gait, stairs and chair only in the hospital)

	Finger dexterity	Nine-hole Peg Test[75] *▪	Moderately high test-retest reliability, high inter-rater agreement and adequate concurrent validity in school-age children[76]	All

	Hand function	Jebsen-Taylor Hand Function Test[77] ▪	Good test-retest reliability in DMD[58] Strongly correlated with muscle strength of the wrist extensors[58], radial deviation range of motion[58] and the Brooke scale[46] in DMD	T2, T4, T5

	Functional status	PEDI[78,79] (selfcare*▪ and mobility*)	Good inter-rater and test-retest reliability[80], content validity[79] and discriminative validity[81] in children with various diagnosis Feasible for evaluative purposes in CP[81,82]	T0, T2, T4, T6/T7*

	Perceived manual abilities	Abilhand[83] ▪ Abilhand-kids[84] *	The Rasch-derived Abilhand is moderately related to grip and key pinch strength, has good test-retest reliability and may be sensitive to change in stroke patients[85] The Abilhand-kids has good test-retest reliability and a higher independence in gross motor function is associated with a higher manual ability in CP[84]	T0, T2, T4, T6/T7*

	Quality of upper-limb motor function	Melbourne Assessment of Unilateral Upper Limb Function[86] (item 1,2,3,10,11 and16) extended with an upper limb motion analysis (Vicon Motion Systems) with 8 cameras▪	The Melbourne Assessment has moderate to high intra- and inter-rater reliability[87] and excellent construct validity in CP[88] A motion capture analysis system can measure task performance with an upper-limb orthosis[45], but soft tissue artefacts may negatively influence accuracy[49]	T2, T4

	Incidence and fear of falls	Semi-structured interview*		All

**Participation**	HRQoL	KIDSCREEN-52[89](child- and parental questionnaire)*▪	Acceptable levels of reliability and validity in children and adolescents[90] Children's most important in their lives generally map well to the items in KIDSCREEN[91]	T0, T2, T4, T6/T7*

**Demographic variables**	Weight and height	Body weight (kg)*▪, standing height* (cm) and arm-span*▪ (cm)		T0*, T2, T4, Y6/T7*

**Co-factors**	Co-interventions	Semi-structured interview*▪		All

	Physical activity	Semi-structured interview (according to the PAQ-C[92] and the 60-min MVPA measure[93])*▪		All

**Symbols:* **= study 1 'Dynamic leg and arm training', ▪ = study 2 'Functional training with arm support'

**Abbreviations**: DMD: Duchenne Muscular Dystrophy; PROM: Passive Range of Motion; ext: extension; dfl: dorsal flexion; abd: abduction; dev: deviation; MRC: Medical Research Council Scale; RF: m. Rectus Femoris; TA: m. Tibialis Anterior; BB: m. Biceps Brachii; FF: forearm flexors; NMD: Neuromuscular Disease; GSGC: Gait, Stairs, Gowers, Chair; PEDI: Pediatric Evaluation of Disability Inventory; CP: cerebral palsy; HRQoL: Health-Related Quality of Life; PAQ-C Physical Activity Questionnaire for older children; MVPA: Moderate-to-Vigorous Physical Activity

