**Methods:**

Study 1 is an explorative randomized controlled trial with multiple baseline measurements. Thirty boys with a DNA-established diagnosis of DMD will be included. The intervention consists of a six-months physical training during which boys train their legs and arms with active and/or assisted cycling training equipment. The primary study outcomes are muscle endurance and functional abilities, assessed with a Six-Minute Bicycle Test and the Motor Function Measure. Study 2 has a within-group repeated measurements design and will include ten boys with DMD who have already been confined to a wheelchair for several years. The six-months physical training program consists of 1) a computer-assisted training and 2) a functional training with an arm support. The primary study outcome is functional abilities of the upper extremity, assessed with the Action Research Arm Test.

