## Methods

### Study 1 Dynamic leg and arm training

#### Design

Study 1 is an explorative randomized controlled trial with multiple baseline measurements. Randomization is stratified according to the ambulatory status (ambulant/non-ambulant) of the boys and the boys are allocated to the intervention group or the control group in a 2:1 ratio. The intervention group receives dynamic exercise treatment, whereas the control group receives usual care (no specific intervention) during 24 weeks. After this period, the control group will also receive the physical training. Randomization is performed by an independent statistician. Despite randomization, differences in baseline characteristics between the intervention group and the control group may still be present due to the relatively small number of participants. For this reason, multiple baseline measurements are performed that will allow us to do within-subject analyses as well. Assessments are not blinded, because it was considered virtually impossible to prevent the boys from revealing their group allocation to the assessor.

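### Table 2 as printed schedules the Six-Minute Bicycle Test, a primary outcome of study 1, at T0, T2 and T5, omitting T4, the visit that closes the randomised 24 weeks

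*Protocol article*

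**What the plan says.** The abstract of the protocol article names two primary outcomes for study 1: "The primary study outcomes are muscle endurance and functional abilities, assessed with a Six-Minute Bicycle Test and the Motor Function Measure". The Primary outcomes section for study 1 describes both.

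Table 2 is introduced as an overview of secondary outcomes, but it also lists both primary instruments. The bicycle test row carries only the study 1 symbol and ends "Feasible for ambulant and non-ambulant boys with DMD (pilot study, unpublished data) T0, T2, T5". The row for the other primary instrument, the Motor Function Measure, says it is done at all assessments.

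The Study outcomes section for study 1 defines the visits. For the intervention arm: "the training period (T3: after 12 weeks; T4: after 24 weeks) and the follow-up (T5: 4 weeks after the end of the training". For the control arm: "the control period (T3: after 12 weeks; T4: after 24 weeks), the subsequent training period (T5: after 12 weeks of training". The same section places T0, T2, T4 and T6 at the hospital, and T5 at home in both arms.

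The Design section gives the control group 24 weeks of usual care and adds: "After this period, the control group will also receive the physical training". The Analysis section plans a two-way ANOVA on the primary outcomes.

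**The concern.** T4 is the last visit at which trained boys can be set against boys who have had only usual care. A primary outcome that skips both T3 and T4 has no value from inside the randomised period. Its single post-baseline value then falls at T5, a label that stands for a different time and a different treatment phase in each arm.

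At stake is the randomised answer on muscle endurance. Under the table, the two-way ANOVA of this outcome would rest on T0, T2 and T5. Its group-by-time contrast would set boys who have recently stopped training against controls midway through theirs. The ultrasonography row (T2, T5, T6/T7) shows the same pattern of T5 without T4.

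**Working it through.** The plan gives no effect size, SD or power for this outcome, so there is no stated figure to reproduce. The check puts the visits on one time axis.

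**Inputs.** From Study outcomes (study 1): T2 at week 8; T4 at 24 weeks into the training or control period; T5 at +4 weeks after training ends (intervention) or +12 weeks into own training (control). From Table 2: bicycle test at T0, T2, T5.

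**Assumptions.** The 24-week period starts at T2, and the controls' training starts at T4.

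| Visit | Intervention: week from T0 | Control: week from T0 | Weeks trained (intervention v control) | Bicycle test in Table 2 |
|---|---|---|---|---|
| T0 | 0 | 0 | 0 v 0 | yes |
| T2 | 8 | 8 | 0 v 0 | yes |
| T3 | 8 + 12 = 20 | 20 | 12 v 0 | no |
| T4 | 8 + 24 = 32 | 32 | 24 v 0 | no |
| T5 | 32 + 4 = 36 | 32 + 12 = 44 | 24, then 4 off v 12 | yes |

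**Gap at T5.** 44 − 36 = 8 weeks. This equals 12 − 4 and does not depend on whether the 24 weeks start at T2.

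**Contrast in training received.** At T4 it is 24 − 0 = 24 weeks. At T5 it is 24 − 12 = 12 weeks. If the effect grew in proportion to weeks trained, which is an assumption made only to give a scale, half of the contrast would be gone at T5 (12/24) before any loss from 4 weeks without training.

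**Direction.** The controls' training, and any loss of effect in the intervention arm after stopping, both shrink the difference. The extra 8 weeks of a progressive disease in controls could widen it. Controls are training during those same weeks, so the pieces cannot be separated and the net sign cannot be worked out from the documents.

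**Within-subject analysis.** The Design section offers this in addition to the between-group comparison. From T2 to T5 the intervention arm covers 24 + 4 = 28 weeks, ending off training. The control arm covers 24 + 12 = 36 weeks, with usual care and training mixed. Both also move from a hospital test at T0 and T2 to a home visit at T5. Neither interval isolates the training period.

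**Is T5 a misprint?** T0, T2 and T4 are all hospital visits and T5 is not. The PEDI, Abilhand and KIDSCREEN rows for study 1 list T0, T2, T4 and T6/T7. Both facts suggest that T4 was meant. Against an isolated slip, the ultrasonography row also has T5 and no T4.

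**The case against.** The strongest reply is that this is a table error and not a design decision. The hospital-visit pattern and the neighbouring rows point that way, and Table 2 has at least one other visible slip (Y6 for T6 in the weight and height row). Figure 4, the dedicated measurement schedule for study 1, is not shown and may list the test at T4. This stands as an explanation. It does not remove the need for correction, because the printed row is the only schedule shown for this primary outcome. If Figure 4 does show T4, the article disagrees with itself.

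A reader might infer that the test is never done at T4. The documents do not support that. Apart from Figure 4, the intervention section says training intensity is set from the Six-Minute Bicycle Test, so controls about to start training would plausibly be tested near T4 unless a T2 value, by then 24 weeks old, were reused. This is an inference, and it supplies no T4 test for the intervention arm.

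A reader might also infer that the trial loses its randomised comparison altogether. That goes too far. The groups at T5 are still the randomised groups, now compared as immediate against delayed training. The Motor Function Measure keeps a T4 comparison, and the study calls itself explorative. What is lost is a clean contrast of training with usual care on one of the two primary outcomes.

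**Conclusion.** The point holds for Table 2 as printed. Followed literally, the table gives no bicycle-test value within or at the end of the randomised 24 weeks. Its only post-baseline value is taken 8 weeks later in controls than in the intervention arm, with 24 v 12 weeks trained instead of 24 v 0. No analysis of T0, T2 and T5 recovers the comparison of training with usual care.

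It is tempting to add that the bias favours the intervention because controls are tested later. The documents do not support a direction: dilution and extra disease time oppose each other, and neither can be sized.

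Weeks 36 and 44 rest on the 24 weeks starting at T2; the 8-week gap does not. Whether the cause is a misprint or an intended schedule is open while Figure 4 is unseen. The correction is needed in either case, because it decides what the trial can conclude on muscle endurance.

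**What to change.** 1. In the bicycle test row of Table 2, replace T5 with T4 in both arms, giving T0, T2 and T4, all hospital visits. Check the row against the Design and Study outcomes sections and Figure 4.
2. In the Analysis section for study 1, name T4 as the visit for the between-arm two-way ANOVA of this outcome.
3. If a bicycle test at T5 or later is also wanted, for example to describe the controls after their own training, state that it serves within-arm description only.
4. In the ultrasonography row, replace T5 with T4 for study 1 only. Keep T6/T7. Leave the study 2 time points as they are: that row serves both studies, and T5 in study 2 is a different visit, 12 weeks after its training ends.

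**Cost.** Items 1 and 2 are text corrections: the T4 hospital visit already takes place, and moving the test adds no procedure. Item 3 costs one more test for each boy in whom it is kept. Item 4 likewise moves a measurement to an existing visit.

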#### Study outcomes

Study outcomes include measurements at the levels of body functions and structures, activities and participation of the ICF[29]. Environmental characteristics (school type and home status) are assessed at baseline. Demographic variables (age, weight, arm span), the use of medication (such as corticosteroids) and any co-interventions are registered during each session.

After a two-month period for baseline measurements (T0: at baseline; T1: after 4 weeks; T2: after eight weeks) to obtain information about the stability of the course of DMD, training with the arm support takes place for six months. Assessments take place after 12 weeks (T3) and 24 weeks (T4) training. Finally, one extra measurement will be done after 12 more weeks (T5) to evaluate to what extent the possible effects of training have lasted. Data is collected by the primary investigator (MJ) at the department of Rehabilitation of the Radboud University Nijmegen Medical Centre (T2, T4), but also at home (T0, T1, T3, T5) to reduce the practical burden on the participants. (figure 7).

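### Table 2 schedules the Study 2 muscle ultrasound at T2 and T5 but not at T4, so the end of training has no scan; T5 may be a misprint for T4

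*Protocol article*

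**What the plan says.** Table 2 (under Secondary outcomes) lists "Quantitative skeletal muscle ultrasonography (muscle thickness and echo intensity") as the measure of muscle atrophy, fibrosis and fatty infiltration. The row carries both study symbols; the table key defines the second as "study 2 'Functional training with arm support". The assessment times are T2, T5 and T6/T7. The last entry carries the Study 1 symbol, and Study 2 has no visit after T5, so Study 2 is left with T2 and T5.

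The Study outcomes section of Study 2 sets the visits. The baseline visits are "T0: at baseline; T1: after 4 weeks; T2: after eight weeks", after which "training with the arm support takes place for six months". It continues: "Assessments take place after 12 weeks (T3) and 24 weeks (T4) training". The purpose of the last visit is then given: "Finally, one extra measurement will be done after 12 more weeks (T5) to evaluate to what extent the possible effects of training have lasted". Visits are held "at the department of Rehabilitation of the Radboud University Nijmegen Medical Centre (T2, T4), but also at home (T0, T1, T3, T5"), so T4 is a hospital visit and T5 a home visit.

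Study 2 has one group and no concurrent controls (Study 2, Design). Its secondary outcomes are analysed like the primary outcome, by a one-way ANOVA of time, or by non-parametric methods (Study 2, Analysis).

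**The concern.** T4 is the visit that shows the state of the muscle after the full training period. T5 is there to show how much of any effect remains. A measure taken at T2 and T5 but not at T4 skips the training-period comparison and also gives T5 nothing to be compared with for retention.

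With two scans, the planned ANOVA of time reduces to one before-after difference. A null result could mean no effect, or a gain that faded during follow-up. A worsening could come from the training period, from the 12 weeks after it, or from disease progression across both. No analysis plan can recover a scan that was never taken, so this has to be settled in the schedule.

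**Working it through.** **1. Study 2 timeline** (Study 2, Study outcomes), in weeks from T0:

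| Visit | Week | Role | Ultrasound in Table 2 |
|---|---|---|---|
| T0 | 0 | baseline | no |
| T1 | 4 | baseline | no |
| T2 | 8 | last baseline visit | yes |
| T3 | 8 + 12 = 20 | 12 weeks of training | no |
| T4 | 8 + 24 = 32 | 24 weeks of training | no |
| T5 | 32 + 12 = 44 | follow-up | yes |

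**2. What the two scans span.** T2 to T5 is 44 − 8 = 36 weeks, of which 24 are training and 12 follow-up (12/36 = 33%). T2 to T4 would be 32 − 8 = 24 weeks, all training.

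**3. What each contrast estimates.** Let E be the training effect at T4, r the share of E that remains at T5, and d the change per week due to the disease, taken as constant. The documents give none of these.

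- T2 to T5 (as printed): rE + 36d
- T2 to T4 (with a T4 scan): E + 24d
- T4 to T5 (if both are scanned): (r − 1)E + 12d

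The printed contrast replaces E by rE and carries 36d − 24d = 12d more progression. Under linear decline that is 36/24 = 1.5 times the drift over the training period.

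**4. Comparison with the other Study 2 rows of Table 2.** Joint mobility, muscle strength, Motor Function Measure, Action Research Arm Test, Brooke scale, Nine-hole Peg Test, co-interventions and physical activity are assessed at all visits. The remaining rows are:

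- Jebsen-Taylor: T2, T4, T5
- PEDI, Abilhand and KIDSCREEN-52: T0, T2, T4 (then T6/T7 for Study 1)
- Melbourne Assessment with motion analysis: T2, T4
- Weight and arm span: T2, T4 (T0 and the last entry carry the Study 1 symbol)

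All of them include T4; ultrasound alone does not. With T4 in place of T5, the ultrasound row would read T2, T4, T6/T7, the same pattern as the PEDI, Abilhand and KIDSCREEN-52 rows apart from T0.

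**The case against.** The strongest reply is that this is a slip in a table and not a design decision. The pattern of the other rows supports that, as does the fact that T4 is a hospital visit. Figure 7, which shows the Study 2 measurements, is not reproduced in the text available, and it might settle the matter. This stands, and it is why the point is put as a conflict to be reconciled. A schedule followed as printed would still lose the T4 scan, and the correction is the same either way.

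A second reply is that moving the scan does not cure the lack of a control group. That is also right: E + 24d cannot be split into training and disease either, and T4 to T5 mixes loss of effect with 12 weeks of progression. A T4 scan confines the contrast to the training period and gives T5 a reference value, but it does no more than that.

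A reader might infer four stronger things that the documents do not support:

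- *That the scans can show no training effect at all.* T2 to T5 can still detect a net effect that persists to T5.
- *That ultrasound is the main check on muscle damage in Study 2.* No section gives it that role. Strength and joint range are assessed at every visit, overstrain questionnaires are completed every two weeks, and adverse events are recorded.
- *That the place of scanning changes between hospital and home.* Visit locations are stated in general; where the ultrasound is done is not.
- *That the 12 weeks after T4 are untrained.* This is implied by the follow-up label and the purpose of T5, but not stated.

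It is also fair that this is one secondary outcome in an explorative study of ten boys, which limits its weight.

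**Conclusion.** The point holds as an inconsistency with a practical consequence. Table 2 gives Study 2 ultrasound at weeks 8 and 44 and none at week 32, when the 24 weeks of training have been completed. The only contrast covers 36 weeks, one third of it follow-up, and cannot separate the end-of-training effect from later loss of effect and 12 further weeks of progression. Retention at T5 cannot be judged without a T4 value.

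This rests on three readings: the row applies to Study 2 (its symbol may cover all four muscles or only the forearm flexors, but Study 2 is included either way); the last entry belongs to Study 1 alone; and the training period ends at T4. The 1.5-fold drift also assumes linear decline. The size of any lost effect cannot be given, because the documents supply neither a rate of change for the ultrasound measures nor a rate at which gains fade. The correction should be made, but it does not touch the Study 2 primary outcome.

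**What to change.** Reconcile Table 2 with the Study 2 visit schedule. Enter T4 for the Study 2 ultrasound, and keep T5 only if retention is of interest. Name T2 to T4 as the training-period contrast, and state that, without a control group, it still includes 24 weeks of disease progression. If T5 is a misprint, replacing the label is enough.

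Moving the scan from T5 to T4 is a table edit with no added scan. Keeping both means one short extra scan per boy at a hospital visit already planned, so at most ten scans in all.

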**Figure 2 F2:**
[figure not shown]
**Progress study 1 Dynamic leg and arm training**. This flowchart is a preliminary version. Final numbers may change depending on eligibility as recruitment is not yet complete.

**Table 1 T1:** Inclusion and exclusion criteria study 1

Inclusion criteria	Exclusion criteria
A DNA-established diagnosis of DMD	Other disabling diseases influencing mobility
Boys who are at the end of their ambulation phase, and: -need ≥5 sec. to get up from the floor or -are not able to get up from the floor or -are not able to bicycle without assistance -are dependent on a wheelchair to move over a long distance (>500 m)	Boys with a clinical symptomatic cardiomyopathy Boys <6 years old
Boys who recently became wheelchair-dependent (approximately 1-2 years after they stopped walking), and: -are able to touch the top of their head with both hands without assistance or -are not able to bicycle without assistance -are able to use a hand-operated wheelchair	

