#### Sample size

The average rate of decline (mean and standard deviation (SD)) of muscle endurance and functional abilities in boys with DMD, as assessed with bicycle ergometry and the Motor Function Measure (MFM), is unknown. Therefore, no sample size can be calculated for these primary outcomes. However, it is anticipated that multiple baseline measurements will increase the chance of finding statistically significant changes in the selected outcome measures. For reasons of convenience, and because this RCT should be regarded as a first explorative study, we decided to include 20 boys in the intervention group and 10 boys in the control group.

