#### Analysis

A two-way analysis of variance (ANOVA) will be used to examine the effects of dynamic leg and arm training on the primary outcomes. Secondary outcomes will be treated similarly or by non-parametric analyses dependent on the type of outcome (interval or ordinal). Data will be analyzed with SPSS version 16.0 and an alpha level of 0.05 will be used to decide on statistical significance.

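### Study 1 routes the timed functional tests, as interval data, to ANOVA, so boys who lose a task after randomisation fall out of that analysis and a difference in decline tends to be understated

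*Protocol article*

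**What the plan says.** Table 2 of the protocol article (Study 1, Secondary outcomes) has a row for functional abilities measured by timed tests. The tool is "Timed and graded functional tests (and total GSGC score"), and the tasks are "walk 10 meters, climb 3 stairs, rise from the floor and rise from a chair". The abbreviation is expanded as "GSGC: Gait, Stairs, Gowers, Chair". In support of the tool, the row says it is sensitive in DMD because "a small reduction in muscle force was accompanied by a large increase in time it takes to complete functional tests". The Discussion (Study outcomes) again names timed tests among the measures chosen for clinical meaning and sensitivity.

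The Study 1 Analysis section applies a two-way ANOVA to the primary outcomes and continues: "Secondary outcomes will be treated similarly or by non-parametric analyses dependent on the type of outcome (interval or ordinal"). It adds that "an alpha level of 0.05 will be used to decide on statistical significance".

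On who is enrolled, Table 1 admits boys at the end of ambulation, including those who "are not able to get up from the floor". The Design section has a non-ambulant randomisation stratum. On size, "we decided to include 20 boys in the intervention group and 10 boys in the control group".

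**The concern.** The routing rule looks only at whether an outcome is interval or ordinal. A time to complete a task is interval while the boy can do the task and undefined once he cannot. Study 1 recruits boys close to that point, so some will have no time at entry and others may lose a task during the 24 weeks.

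Boys without a time at entry are a known group and can be set aside without bias. Boys who lose a task after randomisation are different: losing it is itself an outcome that training may affect. An ANOVA on the remaining times conditions on that outcome, so the arms it compares are no longer the randomised ones. The boys removed tend to be the slowest, and more are removed from the arm that declines faster. That pulls the arms together, whether training slows decline or speeds it.

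There is a second, smaller problem. The row's own rationale says times rise steeply for a small loss of force, so a few very long times just before loss can dominate a mean in seconds.

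**Working it through.** The article gives no mean, SD or rate of task loss for these tests, so there is no planned figure to reproduce. The size can only be illustrated, and every input in steps 2 and 3 is an assumption.

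**1. Which analysis applies.** Seconds are interval, so the Analysis section sends them to ANOVA. Grades are ordinal, so they go to a non-parametric method. The row contains both. The ANOVA on times therefore follows from the stated rule, and it runs beside the graded analysis.

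**2. Five-boy example (assumed 10 m times 7, 9, 11, 14, 20 s).** All slow by 20% and the slowest stops walking.
- Mean time before: (7 + 9 + 11 + 14 + 20)/5 = 12.2 s.
- Mean time after, four boys: 1.2 × (7 + 9 + 11 + 14)/4 = 12.3 s.
- Same four boys, paired: 10.25 to 12.3 s (+20%).
- Mean speed before: (10/7 + 10/9 + 10/11 + 10/14 + 10/20)/5 = 0.93 m/s.
- Mean speed after, with 0 for the boy who is unable: 0.69 m/s (−26%).

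The flat unpaired mean comes from comparing five boys with four. A paired analysis shows the slowing of those who remain, but still contains nothing from the boy who lost the task.

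**3. Two-arm illustration.** Assumed: baseline times log-normal with median 11 s and log SD 0.4; 30% slowing in controls and 10% in trained boys; no further within-boy variation; unable above 25 s. The T4 medians are 14.3 s and 12.1 s.
- Difference if every boy could be timed: 11 × exp(0.4²/2) × (1.3 − 1.1) = 2.4 s (2.38).
- Proportion above the limit, 1 − Φ(ln(25/median)/0.4): controls 1 − Φ(1.40) = 8%; trained 1 − Φ(1.81) = 3.5%.
- Mean of those still timed, median × exp(0.08) × Φ(z − 0.4)/Φ(z) with z = ln(25/median)/0.4: controls 14.2 s, trained 12.5 s.
- Completers' difference in T4 means: 14.17 − 12.51 = 1.7 s (1.66). 1.66/2.38 = 0.70, so 30% too small.
- Completers' difference in change: (0.3/1.3) × 14.17 − (0.1/1.1) × 12.51 = 3.27 − 1.14 = 2.1 s (2.13). 2.13/2.38 = 0.90, so 10% too small.

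About 2% of boys already exceed the limit at baseline (1 − Φ(2.05)). Among boys able at baseline, 6% of controls and 1.5% of trained boys become unable. The full difference is then 2.31 s, and the shortfalls are 28% (1.66/2.31) and 8% (2.13/2.31), essentially the same range.

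**4. Scale in this trial.** If all 30 boys could do the task at entry, these rates mean about 10 × 0.08 = 0.8 controls and 20 × 0.035 = 0.7 trained boys above the limit. The numbers are small, but so are the arms, and actual rates near the end of ambulation could be higher or lower.

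**The case against.** The strongest reply is that the row does not measure times alone. It opens with timed and graded tests and a total GSGC score, and graded data have their own non-parametric route. Loss of function can also register on the Vignos scale, the Functional Mobility Scale and the MFM, which is a primary outcome and applies to ambulant and non-ambulant patients. This stands. A reader might infer that the worst decline vanishes from the trial's comparison, or that harm from training would be hidden. The documents do not support that. The article does not define the grade levels, so how inability is graded cannot be stated; equally, it cannot be said that inability goes unrecorded.

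What does not stand is that these scores repair the analysis of the times. They are separate outcomes, and the article presents the times as an endpoint in their own right.

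A second reply is that a missing coding rule is silence, of the kind an article leaves to its full protocol or analysis plan. A fuller document may well contain such a rule. The point here is narrower: the article does state a rule, by data type, and that rule applied to seconds leads to the selected comparison.

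A third reply is that the size rests on invented inputs and that the flat mean in the five-boy example disappears on pairing. Both are correct. The direction survives; the exact size does not.

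**Conclusion.** The point holds in a limited form. Under the stated routing rule, the ANOVA on the timed tests uses only boys still able to do the task, which is a selection made after randomisation, and it tends to understate a between-arm difference in decline. Under the assumed inputs the understatement is roughly 10 to 30%, depending on whether changes or T4 values are compared. That range is illustrative and carries no authority for this trial's actual rates.

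The defect affects one component of one secondary outcome in a trial described as explorative. The primary outcomes and the graded measures are untouched. It rests on reading times as interval outcomes and on some boys losing a task by T4; if none did, no post-randomisation selection would arise.

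**What to change.** For each task, among boys able to do it at baseline, analyse speed (m/s for the walk, stairs/s for the stairs, 1/time for rising) with 0 for attempted and unable. Compare T4 between arms, adjusted for baseline speed. A rank test with unable as the worst rank is an acceptable alternative. Report boys unable at baseline separately for each task, list raw times descriptively, and do not test them by ANOVA on completers. A missed or unattempted test should stay missing and not be scored 0.

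The cost is analysis wording. T0, T2 and T4 are all hospital visits in both arms, so walking, stairs and chair are already scheduled at the visits needed, and the floor rise is scheduled at every visit. The downside is that speeds are less familiar than seconds, which the listing of raw times offsets.
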